### **7.3 Summary of findings from clinical studies**

Not applicable

### **7.4 Summary of known and potential risks and benefits**

Not applicable

### **7.5 Description and justification of route of administration and dosage**

Not applicable

### **7.6 Dosages, dosage modifications and method of administration**

Not applicable

### **7.7 Preparation and labelling of Non Investigational Medicinal Product**

Not applicable

### **7.8 Drug accountability**

Not applicable

## 8. METHODS

### 8.1 Study parameters/endpoints

#### 8.1.1 Main study parameter/endpoint

The main outcome parameters are symptomatic urinary tract infection (sUTI) and hospital admission due to this sUTI. The definition of a sUTI used for this trial is based on the criteria of Woodford et al (29), on the basis of the EAU guidelines on Neurourology (3) and on the basis of the NHG Guidelines for general practitioners (27).

1. Symptomatic UTI (sUTI): A patient with an acute onset of one or more of the following symptoms: dysuria/pain during catheterization, hematuria, frequency, urgency, urinary retention, suprapubic pain, flank pain, fever, delirium or rigors who did not have a negative urine culture result or a negative nitrite test or a negative dipslide/urine sediment (when taken before receiving antibiotics) or a positive blood culture for a known uropathogen. Additionally, in patients with neurogenic bladder a change in specific symptoms, like increase in incontinence, limb spasm and autonomic dysregulation, could be indicative for a sUTI. The diagnosis is to be decided by the local consultant involved in study.

2. Bacteremic UTI (bUTI): A patient with a blood culture positive for a known uropathogen, providing that their urine culture was not negative (when taken before receiving antibiotics).

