## 2. OBJECTIVES

The aim of this trial is to compare single use vs reusable catheters in clean intermittent catheterization and to find out if reusing catheters is not less safe and not less efficient as the current single use practice, leading to the following objectives:

Primary Objective:

1. To determine whether reusable catheters are at least not less safe as single use catheters, measured by symptomatic UTIs.

Secondary Objectives:

1. To register hospital admissions due to UTIs or other adverse events due to CIC.
2. To register other adverse events like the number of urethral damage/strictures and kidney/bladder stone formation in both groups.
3. To determine whether reuse of catheters leads to changes of the urine cultures/urinary microbiome (in cooperation with the department of Medical Microbiology).
4. To perform economical evaluation of the cost-effectiveness of single use versus reusable catheters.
5. To explore patients' perspective on ease of use and cleaning of the reusable catheters compared to the single use catheters.
6. To formulate conclusive recommendations for health care providers and re-formulations of existing protocols.

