## 10. STATISTICAL ANALYSIS

### 10.1 Primary study parameters

For analysis of the results, the groups will be stratified for gender and the female patient group will be balanced for pre- and post-menopausal. Data analysis will be performed using SPSS. The primary analysis will be to assess difference between the intervention and the control groups in the sUTI rate and other adverse effects. Descriptive statistics will be used to describe baseline characteristics of participating patients in both groups. Binomial or categorical outcome measures will be analyzed using Chi-square tests and quantitative outcome variables by t-tests or Mann-Whitney U tests. Two-sided p values are calculated.

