#### 2.3.2 Secondary Objectives

# STATISTICAL ANALYSIS PLAN for COMPaRE-trial

Our secondary objectives are to investigate the efficiency and costs-effectiveness of the reusable catheter and to explore patient opinions on the reusable catheter. The table below provides an overview of all objectives and outcome measures.

| Objectives                                                                                                                        | Primary outcome | Secondary outcome                                                                                                                                                                                                                                                          | Measured by                                                                                                                                                                                                                  |
|-----------------------------------------------------------------------------------------------------------------------------------|-----------------|----------------------------------------------------------------------------------------------------------------------------------------------------------------------------------------------------------------------------------------------------------------------------|------------------------------------------------------------------------------------------------------------------------------------------------------------------------------------------------------------------------------|
| Safety
To determine whether reusable catheters are at least not less safe as single use catheters                       | No of sUTIs     | 
 
▶ Hospitalisation due to a sUTI
 
▶ Bacteraemic UTI
 
▶ Urethral damage leading to clinical significant strictures
 
▶ Kidney/bladder stone formation
 
▶ Episodes of macroscopic haematuria
 
 | 
 
▶ sUTI (see definition)
 
▶ sUTI +hospitalisation records
 
▶ sUTI +positive blood culture
 
▶ Anamnestic
 
▶ Anamnestic
 
▶ Anamnestic
 
 |

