### 3.3.2 Confidence Intervals and p-values

All calculated p-values will be two-sided and compared to a 5% significance level. If a p-value is less than 0.05, the corresponding treatment group difference will be denoted as statistically significant. All efficacy estimates will be presented with two-sided 95% confidence intervals. As there is only one primary null hypothesis to be tested in this trial, there will be no adjustments for multiplicity.

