### 3.3.3 Decision Rule

This trial is designed to address a single primary outcome. Non-inferiority is claimed if the primary null hypothesis is rejected on the significance level (alpha) of 0.025 (one-sided). That is, if the upper-limit of the two-sided 95% confidence interval for the treatment difference is less than 7%.

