### Overview of Outcomes

| Level     | Outcome                        | Timeframe    | Type        |
|-----------|--------------------------------|--------------|-------------|
| Primary   | UTIs per month                 | During trial | Continuous  |
| Secondary | UTI during follow-up           | During trial | Dichotomous |
|           | Hospitalisation due to UTI     | During trial | Dichotomous |
|           | Bacteraemic UTI/ urosepsis     | During trial | Dichotomous |
|           | Urethral stricture             | During trial | Dichotomous |
|           | Bladder/kidney stone formation | During trial | Dichotomous |
|           | Epididymo-orchitis             | During trial | Dichotomous |
|           | Prostatitis                    | During trial | Dichotomous |

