## 6.1.4 Methods (S)AE Primary Outcomes

### 6.1.4.1 Descriptive Statistics

The frequency (n) and percentage (%) of subjects with any (s)AEs will be summarised by treatment group. SAEs will be detailed and presented in a separate table.

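### Hospital admission for sUTI is labelled a main outcome in one section and secondary elsewhere, and the serious harms under the not-less-safe objective have no planned between-arm estimate or confidence interval

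*Combined protocol and SAP*

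**What the plan says.** **Status of hospital admission**

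- Protocol 8.1.1: "The main outcome parameters are symptomatic urinary tract infection (sUTI) and hospital admission due to this sUTI".
- Protocol section 2 places admission first among the secondary objectives: "To register hospital admissions due to UTIs or other adverse events due to CIC". The protocol summary also counts it as secondary.
- SAP 2.3.2 puts it in the secondary-outcome column, and the SAP overview of outcomes lists it as a secondary, dichotomous outcome.
- SAP 3.3.3: "This trial is designed to address a single primary outcome". The rule that follows applies to the monthly UTI rate, with a 7% margin.

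**Objective and methods for the serious harms**

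- The safety row of the SAP 2.3.2 table reads: "To determine whether reusable catheters are at least not less safe as single use catheters". Its secondary outcomes are admission, bacteraemic UTI, stricture, stones and macroscopic haematuria.
- Protocol 10.1: "Binomial or categorical outcome measures will be analyzed using Chi-square tests and quantitative outcome variables by t-tests or Mann-Whitney U tests". The p values are two-sided.
- SAP 3.3.2: "If a p-value is less than 0.05, the corresponding treatment group difference will be denoted as statistically significant". The same section promises 95% intervals for efficacy estimates.
- SAP 6.1.4.1: "The frequency (n) and percentage (%) of subjects with any (s)AEs will be summarised by treatment group". SAP 7.1 repeats this and adds a separate SAE table.
- The SAP table of contents announces a methods section for (S)AE secondary outcomes. In the body, section 6.2 opens with the questionnaires and no such section follows.

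**The concern.** Two things do not fit together.

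First, a reader of protocol 8.1.1 would expect admission to carry a confirmatory conclusion, while a reader of the protocol objectives or the SAP would not. No sentence resolves this, so it is unclear how far a successful non-inferiority result is meant to reach.

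Second, the question asked of the serious harms is whether reuse is not worse. A two-sided test of no difference does not answer that. When events are few, a non-significant result is the likely outcome whether or not reuse is harmful. Bare percentages leave the reader to work out the uncertainty. The informative quantity is the largest excess risk that the data have not ruled out, and neither document asks for it.

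Urosepsis is the only SAE that the protocol expects (9.2.2). No DSMB and no interim analysis are planned (protocol 9.5 and 10.4). The final comparison is therefore the main between-arm look at severe infection, and its method is the least specified.

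**Working it through.** **1. Sample size used as input.** Protocol 4.4 and SAP 6.3 give 154 effective cases per arm, inflated for 20% dropout.

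- 154 / 0.80 = 192.5, rounded up to 193 per arm, so 386 in total. This reproduces.
- The stated formula with the printed margin of 0.11 gives (1.960 + 0.842)² × (0.26×0.74 + 0.29×0.71) / (0.26 − 0.29 − 0.11)² = 7.849 × 0.3983 / 0.0196 = 159.5, so 160. A margin of 0.1125 gives 7.849 × 0.3983 / 0.0203 = 153.95, so 154. The unrounded margin is my inference. It does not affect this point, which needs only the planned numbers.

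Follow-up stops at withdrawal (protocol 8.6), while the ITT set in SAP 4.5 keeps everyone who started treatment. The effective size therefore lies between 154 and 193 per arm.

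**2. Event rate.** Neither document gives a rate of admission or of any other serious harm. Protocol 12.2 expects complications of participation to be infrequent, which is not a background admission rate. I assume 12-month control risks from 1% to 10%.

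**3. Chance of missing a doubling.** The test is the uncorrected Chi-square, z = (x₂ − x₁)/n ÷ √(2p̄(1 − p̄)/n), where x₁ and x₂ are the event counts on single-use and reusable catheters and p̄ = (x₁ + x₂)/(2n). Power is the exact binomial probability that z > 1.96 in the harmful direction. The miss rate is 1 minus power.

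| Control → reusable risk (assumed) | Power, 154/arm | Missed | Power, 193/arm | Missed |
|---|---|---|---|---|
| 1% → 2% | 0.092 | 91% | 0.110 | 89% |
| 2% → 4% | 0.158 | 84% | 0.201 | 80% |
| 3% → 6% | 0.239 | 76% | 0.292 | 71% |
| 5% → 10% | 0.379 | 62% | 0.469 | 53% |
| 7% → 14% | 0.526 | 47% | 0.622 | 38% |
| 10% → 20% | 0.699 | 30% | 0.795 | 20% |

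By the normal approximation, power passes 50% at a control risk of about 6.8% (154 per arm) or 5.5% (193 per arm). It reaches 80% at about 12.4% or 10.3%.

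**4. What an interval would show.** Suppose 3 admissions occur in each arm of 154 (1.9% each).

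- Risk difference: the Wilson limits for 3/154 are 0.66% and 5.57%. The Newcombe upper limit is √((5.57 − 1.95)² + (1.95 − 0.66)²) = 3.8 points.
- Risk ratio: exp(1.96 × √(2 × (1/3 − 1/154))) = exp(1.585) = 4.9.

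If the true risks are equal, the approximate upper limits are:

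| Risk in both arms (assumed) | Difference, 154 / 193 per arm | Ratio, 154 / 193 per arm |
|---|---|---|
| 1% | +2.2 / +2.0 points | 9.2 / 7.3 |
| 2% | +3.1 / +2.8 points | 4.8 / 4.0 |
| 5% | +4.9 / +4.3 points | 2.6 / 2.4 |

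On the ratio scale a doubling stays inside the interval in every row.

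**The case against.** The strongest reply is that the non-inferiority claim is already confined to the UTI rate. The primary objectives of both documents are measured by UTIs, the hypotheses and decision rule in SAP 3.3 concern the monthly rate alone, and protocol section 2 only sets out to register admissions and other harms. Much of this stands. It makes the 8.1.1 label an inconsistency to be reconciled, not a second confirmatory endpoint left without a test.

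Four stronger readings are tempting and are not supported:

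- **That these harms are judged solely by a p<0.05 test.** The Chi-square comes from a general paragraph in protocol 10.1, and SAP 3.3.2 is a general convention. For (S)AEs the SAP specifies counts and percentages, and hospitalisations are normally SAEs.
- **That the test misses a doubling most of the time, without condition.** This depends on a rate that the documents do not give, and it fails above a control risk of roughly 5.5% to 6.8%.
- **That the trial plans to report a null result on admission as proof of safety.** No passage says so.
- **That 3 against 3 admissions leaves open an increase of just under threefold.** Adding 3.8 points to a 2% control estimate is not a ratio bound. The ratio limit is about 4.9.

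It is also fair to say that low power for rare secondary harms is inherent in a trial sized on its primary outcome, that an interval does not cure it, and that a reader could calculate one from the published counts. That limits the gain to clearer reporting. It does not defend a test of no difference as the stated method for a question of whether reuse is worse.

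**Conclusion.** The point holds as a low-cost improvement. Two facts come straight from the documents: the status of hospital admission is inconsistent between protocol 8.1.1 and the rest of the plan, and no between-arm estimate or interval is specified for the serious harms listed under the not-less-safe objective.

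The size is conditional. With an assumed 12-month control risk of 1% to 5%, the protocol's Chi-square test would miss a doubling 91% to 62% of the time at 154 per arm and 89% to 53% at 193. At 10% the miss rates fall to about 30% and 20%. The primary analysis of the UTI rate is unaffected.

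**What to change.** 1. Reconcile protocol 8.1.1 with the protocol summary, protocol section 2, SAP 2.3.2 and SAP 3.3.3. State that the non-inferiority conclusion applies to the monthly UTI rate only.
2. In SAP 6.1.4 and section 7, for hospitalisation due to UTI, bacteraemic UTI, stricture and stones, report the risk difference (reusable minus single-use) with a two-sided 95% score or exact CI beside the counts, in place of a superiority p value or counts alone. Describe the upper limit as the largest increase not excluded.

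The cost is SAP wording and a few table columns, with no new data. The downside is visibly wide limits for rare harms. The change adds no power: 80% power for a doubling from an assumed 5% would need 435 per arm, and from 2% would need 1,141. At low event rates the intervals will still include a doubling, and the report should show that openly.

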## **8.2 Randomisation, blinding and treatment allocation**

Patients who sign informed consent will be randomised into the intervention or in the control group. Randomisation will be performed using the program ALEA, which is the program used in the Erasmus MC. ALEA is developed for randomisation and guarantees concealed allocation. The groups will be stratified for the participating centres, neurogenic and non-neurogenic causes for catheterization, age (16-17 years vs.  $\geq 18$  years and  $< 50$  years vs.  $\geq 50$  years old), gender, and the female patient group will be balanced for pre- and post-menopausal status. There is no ability for blinding in this trial.

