## **8.3 Study procedures**

This study will be a prospective non-inferiority trial with two randomized groups. The patients will be screened, included and randomized at the outpatient clinic of the participating hospital departments. One group of patients will use the reusable catheter and the control group will use the single use catheters. After inclusion, the patients will be followed up for a period of twelve months. See chapter 3 'Study design' for the precise follow up schedule.

There will be two extra clinical consults and seven telephone consults when participating in this study. Patients will receive a financial compensation for the expenses of traveling to the hospital for the clinical consultations.

Tracking UTIs and hospital admissions will be performed by status analysis by the researchers of the trial and patients will track their infections using a diary. Active cooperation of the involved consultants and continence nurses is asked when the participating centers are included in the trial. For the contact moments, standardized

questions will be provided in Gemstracker, so all patients will be asked the same questions and data will be as complete and similar as possible.

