### 5.2 Primary Outcome Definition

The primary outcome is the monthly incidence of UTIs during the study period. The definition of a UTI used for this trial is based on the criteria of Woodford et al (1), on the basis of the EAU guidelines on Neurourology (2) and on the basis of the NHG Guidelines for general practitioners (3).

An UTI is defined by the following two criteria:

1. An acute onset of one or more of the following symptoms: dysuria/pain during catheterization, hematuria, urinary frequency, urinary urgency, suprapubic pain, flank pain, fever ( $>38^{\circ}\text{C}$ ), rigors, and delirium. In case of a neurogenic bladder: a change in specific symptoms, like increased urinary incontinence, limb spasm and autonomic dysregulation, could be indicative for a UTI.
2. One of the following positive diagnostic tests: urine culture, dipslide, nitrite test, or urine sediment analysis.

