### 5.3.5 Episode of macroscopic hematuria

An episode of macroscopic hematuria refers to any occurrence of visible blood in the urine during the study period. Each distinct occurrence (even if it recurs after a period of absence) will be counted as a separate episode.

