## 6.1.2 Primary Analysis

For the primary outcome, the incidence rate in each group is the total number of UTIs divided by the total follow-up time, reported with 95% confidence intervals calculated using bootstrap procedure. The absolute difference between groups will be calculated and reported with a 95% bootstrap confidence interval. Non-inferiority will be concluded if the upper limit of the CI is below the non-inferiority margin of 7%. The incidence rate ratio (IRR) with a 95% CI will be estimated in both arms using a poisson or negative binomial regression model (in case there is overdispersion of the data). All analyses will be conducted using R version 4.2.1 (R Foundation for Statistical Analysis, Vienna, Austria).

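### Primary UTI events are classified unmasked in an open-label trial, under two conflicting definitions and with no new-episode rule, so knowledge of the arm can move the count that decides non-inferiority

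*Combined protocol and SAP*

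**What the plan says.** - **Who decides.** Protocol 8.1.1 defines the symptomatic UTI and then states: "The diagnosis is to be decided by the local consultant involved in study". SAP 5.2 does not repeat this, but SAP 2.1 presents the SAP as a supplement to the protocol, so the consultant's role is not withdrawn.
- **Masking.** Protocol 8.2: "There is no ability for blinding in this trial".
- **Capture.** Protocol 8.3, in a sentence that closes by naming a diary: "Tracking UTIs and hospital admissions will be performed by status analysis by the researchers of the trial and patients will track their infections using a". Standardised questions are asked at the contacts, but their content is not shown.
- **Test requirement, protocol 8.1.1.** A symptomatic patient "who did not have a negative urine culture result or a negative nitrite test or a negative dipslide/urine sediment" (if taken before antibiotics), or has a positive blood culture.
- **Test requirement, SAP 5.2.** Besides an acute symptom: "One of the following positive diagnostic tests: urine culture, dipslide, nitrite test, or urine sediment analysis". For a neurogenic bladder, certain symptom changes "could be indicative for a UTI".
- **What is counted.** SAP 6.1.2: "the incidence rate in each group is the total number of UTIs divided by the total follow-up time". Non-inferiority is concluded if the upper 95% limit for the difference is below 7% (SAP 3.3.3 and 6.1.2).
- **Episodes.** For macroscopic haematuria, a secondary outcome, SAP 5.3.5 says: "Each distinct occurrence (even if it recurs after a period of absence) will be counted as a separate episode". Neither document has a corresponding sentence for UTI.

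**The concern.** Blinding is impossible for patients and those who care for them. That does not make it impossible to classify an event from recorded symptoms, dates and test results with the arm code removed, and neither document plans this. The people who decide whether a borderline report counts, and whether a second report is a new infection, can be expected to know the arm.

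Attention to infection is also unlikely to be symmetric. Protocol 6.4 and 11.4 name UTI as a risk of reuse. The cleaning checks in the section 3 schedule, and the exclusion for persistently incorrect cleaning in 8.4.1, bear on reusable-catheter users.

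The primary estimate is a rate of all events, so both decisions feed directly into the quantity compared with the margin. Under-counting in the reusable arm favours a false claim of non-inferiority; over-counting there works against a true one.

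**Working it through.** **1. The two definitions side by side.**

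| Element | Protocol 8.1.1 | SAP 5.2 |
|---|---|---|
| Test | No negative result, or a positive blood culture | At least one positive urine test |
| Symptomatic patient with no test done | Can qualify | Does not qualify |
| Urinary retention as a symptom | Listed | Not listed |
| Who decides | Local consultant | Not stated |
| Neurogenic symptom changes | Possible indicator | Possible indicator |
| New versus continuing UTI | Acute onset only | Acute onset only |

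A report can therefore be an event under one document and not the other. Routine urine samples are taken only at weeks 0 and 52 (SAP 5.1.2), so qualifying tests in between are requested in unmasked care.

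**2. The plan's own figure.** Inputs from protocol 4.4 and SAP 6.3: rates 0.13 and 0.14 per month, SD 0.21, one-sided alpha 0.025, power 0.80, margin set at 50% of the means. The formula is n = 2·SD²·(1.960 + 0.842)²/d².
- d = 0.5 × 0.135 = 0.0675 gives 151.9, so 152 per arm, as stated.
- d = 0.07, the limit in the decision rule, gives 141.3, so 142.

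The 152 thus rests on the unrounded margin. Below I use 152 per arm and the decision limit 0.07.

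**3. Scale.** At 152 × 12 patient-months, 0.13 per month is about 237 UTIs and the margin is about 128. At 0.20 per month the reusable arm has about 365, so 10% of its events is about 36.

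**4. Decision threshold.** SE = 0.21 × √(2/152) = 0.0241. Success requires an observed difference below 0.07 − 1.96 × 0.0241 = 0.0228.

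**5. One-arm miscounting.** P(success) = Φ((0.0228 − D)/0.0241), where D is the expected observed difference. The documents give no miscount rate, so 5% to 20% is an assumption.

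| Share f of reusable-arm events | True 0.20 v 0.13, undercount: D = 0.20(1 − f) − 0.13 | False success | True 0.13 in both, overcount: D = 0.13f | Success |
|---|---|---|---|---|
| 0 | 0.070 | 2.5% | 0 | 82.8% |
| 5% | 0.060 | 6.1% | 0.0065 | 75.1% |
| 10% | 0.050 | 12.9% | 0.013 | 65.8% |
| 20% | 0.030 | 38.2% | 0.026 | 44.7% |

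**6. Check with counts.** I simulated overdispersed 12-month counts with the same means and SD, 20,000 replicates and a normal-theory interval (not the SAP's bootstrap). False success was 2.2%, 5.8%, 12.6% and 44.0% for undercounts of 0, 5, 10 and 20%. With equal rates and the same shares of reusable-arm events counted twice, success was 82.5%, 72.7%, 62.0% and about 39%.

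**7. Episode rule without arm bias.** Merging 10% of events in both arms at the margin gives D = 0.9 × 0.07 = 0.063 and Φ((0.0228 − 0.063)/0.0241) = 4.8%. The simulation also gives 4.8%, and 10.6% when 20% are merged. Double counting 10% in both arms at equal rates lowers simulated success to about 75%.

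**The case against.** The strongest reply is that SAP 5.2 is the definition used for analysis, that it requires a symptom and a positive test, and that it does not mention the consultant. That is a real safeguard. A reader of protocol 8.1.1 alone might infer that the primary event is simply an unmasked opinion; SAP 5.2 does not support that, and even isolated neurogenic symptoms need a positive test there. What remains is that no one is named to apply the rule, the protocol's sentence still stands, and the two definitions differ.

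The acute-onset wording argues against counting a retest or a second antibiotic course without new symptoms, and the haematuria sentence sets no interval either. Both points are fair, so the contrast with haematuria should not be pressed. Neither says when a second symptomatic, test-positive report is new, or how diary and hospital reports of one infection are matched. The yes/no outcome of any UTI during follow-up (SAP overview of outcomes) is immune to double counting, but it is secondary and does not decide the trial.

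The most important limit is that knowledge of the arm also affects reporting symptoms, seeking care and ordering tests. Removing the arm code later leaves all of that in place. A reader might take the 13% and 38% as the gain from masked classification; they are not.

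**Conclusion.** The point holds and should be acted on. The plan leaves classification and counting of the primary event unmasked, under two definitions that must be reconciled, with no rule for repeat events. Even an assumed 5% one-arm undercount would more than double the 2.5% error at the margin, to about 6%.

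These figures are illustrative. They assume error in one arm and one direction, SD 0.21, 152 per arm and a normal approximation. That the consultant knows the arm is inferred from the absence of blinding, not stated. One might also infer that the design is tilted towards declaring non-inferiority. The documents do not support a direction: heightened vigilance in the reusable arm would push the other way.

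**What to change.** 1. Reconcile protocol 8.1.1 and SAP 5.2 into one definition, stating that the SAP's symptom-plus-positive-test rule defines the primary event.
2. For the primary count, replace the consultant's decision with programmed application of that rule to an extract without the arm code. Existing staff read records that need judgement, such as neurogenic symptom changes, also without the arm code. Keep the consultant's diagnosis as a supportive analysis; patient care is unaffected.
3. Before any by-arm data are seen, fix one episode rule, for example a minimum interval between symptom onsets, with diary and hospital reports of the same infection merged. Repeat with a shorter interval, a longer interval and no merging.
4. Confirm that symptom onset, test type, test date and test result are captured. The documents do not list these fields.

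The cost is wording in two sections and a derivation program, with no added visits or tests. If the fields in item 4 are incomplete, they would have to be retrieved from source records. Some clinically diagnosed UTIs will be merged or not counted. Merging also makes a fixed 0.07 margin easier to meet (about 4.8% false success if 10% are merged in both arms), so the no-merging result must be reported beside the main one.
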